## Abstract

**Background:**

Hypertension control remains a major global challenge. The behavioral approaches recommended for blood pressure reduction are stress reduction, increased exercise and healthy dietary habits. Some study findings suggest that yoga has a beneficial effect in reducing blood pressure. However, the role of yoga on blood pressure has received little attention in existing health care practices in developing countries. This study will be conducted in primary health care facilities in Nepal to assess the effectiveness of a pragmatic yoga intervention to complement standard practice in further reducing blood pressure.

**Methods:**

This will be multicentric, two arms, randomized, nonblinded, pragmatic trial. It will be conducted in seven District Ayurveda Health Centers (DAHCs) in Nepal between July 2017 and June 2018. The study participants will consist of hypertensive patients with or without antihypertensive medication attending to the outpatient department (OPD). One hundred and forty participants will be randomized to treatment or control groups by using a stratified block randomization. At the study site, the treatment arm participants will receive an intervention consisting of five days of structured yoga training and practice of the same package at home with a recommendation of five days a week for the following 90 days. Both the intervention and control groups will receive two hours of health education on lifestyle modifications. The primary outcome of this trial will be the change in systolic blood pressure and it will be assessed after 90 days of the intervention.

**Discussion:**

This study will establish the extent to which a yoga intervention package can help reduce blood pressure in hypertensive patients. If proven effective, study findings may be used to recommend the governing bodies and other stakeholders for the integration of yoga in the national healthcare system for the treatment and control of hypertension.

**Trial registration:**

Clinical Trial Registry- India (CTRI); CTRI Reg. No- CTRI/2017/02/007822. Registered on 10/02/2017.

## Background

Hypertension is a major public health issue worldwide. Globally, 874 million adults had systolic blood pressure (SBP) of 140 mmHg or higher in 2015 [1]. Recent evidence suggested that nearly one third of Nepali had high blood pressure [2]. Hypertension is one of the established risk factors for stroke, myocardial infarction, congestive heart failure, arterial aneurysm and chronic renal failure [3]. Risk of cardiovascular disease multiplies for each 20/10 mmHg increment of systolic/diastolic blood pressure above normal blood pressure cut-offs [4].

Prevention and management of hypertension is a global public health challenge. Apart from antihypertensive medicines, lifestyle modifications have been recommended as an equal first line approach for controlling hypertension [4, 5]. Healthy lifestyle such as weight loss, dietary sodium and total fat reduction, limiting alcohol intake, increased intake of vegetables and fruit, quitting smoking and regular physical exercise may lower SBP in the range of 4–9 mmHg [5, 6].

Use of complementary and alternative medicine (CAM) for treating high blood pressure is becoming increasingly popular [7]. A trial conducted in Thailand demonstrated that yoga treatment was associated with significant reduction in blood pressure compared with the control group (SBP: mean difference − 26.74 mmHg; diastolic blood pressure (DBP): − 19.80 mmHg) [8]. Deepa et al. found a significant fall in mean blood pressure after three months of yoga practice (*p* < 0.00001) (SBP: -9.92 mmHg; DBP: − 9.83 mmHg) among the mild to moderate essential hypertensives [9]. Similarly, a study conducted in eastern Nepal reported that yoga significantly reduced the blood pressure level (SBP: 144 mmHg Vs 130 mmHg; *p* = 0.018, and DBP: 98 mmHg Vs 88 mmHg; p = 0.018) among the essential hypertensive participants [10]. In a Cochrane review conducted by Hartley L et al., yoga was found to significantly lower DBP (Mean deviation − 2.9 mmHg, 95% CI -4.52 mmHg to − 1.28 mmHg) [11]. However, out of 11 studies analyzed, six studies confirmed that there was no significant reduction in SBP and one study, in contrast, reported an increase (Mean deviation 2.2 mmHg) in SBP [11]. A definite conclusion over the therapeutic use of yoga as an adjunct to hypertension therapy is lacking because of inconsistency in findings as well as non-uniformity in yoga prescription [12–14]. Moreover, these systematic reviews have recommended for larger and methodologically sound studies to determine the impact of yoga on hypertension [12–14].

This study aims to assess the effectiveness of structured yoga program in reducing blood pressure level in hypertensive patients attending DAHCs in Nepal. The study will be conducted in real-world clinical practice settings, with typical patients and by government health workers, who are not the professional yoga instructors. If the study finding is significant, yoga may be integrated as a complementary therapy for hypertension management in public health facilities in Nepal.

## Primary objectives

The primary objective of the study is to assess the effect of structured yoga practice on blood pressure reduction among people with hypertension attending the primary healthcare facilities. This study will determine whether practicing yoga leads to a clinically relevant reduction in blood pressure. Both clinic management and follow-on home-based yoga practice among hypertensive participants will be in the prescribed program. The outcome will be the change in systolic blood pressure at 90 days. We will also record the change in diastolic blood pressure. The secondary aim of the study is to assess the effect of yoga in reducing body mass index among the same participants.

## Methods

### Trial design

This study will be conducted among 140 hypertensive participants in seven District Ayurveda Health Centers in Nepal. It will be a randomized, two-armed, non-blinded, pragmatic trial.

### Study settings

This study will be conducted in seven purposively selected DAHCs in Nepal. Currently, two centrals, 14 Zonal and 61 District Ayurveda Health Centers are catering preventive, promotive & curative primary healthcare services throughout Nepal under Department of Ayurveda (DoA), Ministry of Health, Nepal. Recently, DoA has initiated Training of Trainers (ToT) of yoga to capacitate its technical staffs (Ayurveda doctors and paramedics working at DAHC) to educate the patients and community on basic yoga skill. The main objective of ToT is to integrate and promote yoga within Ayurveda health system for health promotion and disease prevention. This study will orient and mobilize the trained DAHC human resources to deliver yoga interventions for the hypertensive participants those attending primary healthcare centers.

This study has purposively selected seven DAHCs from the following districts: Ramechhap, Dhading, Nuwakot, Kaski, Rupandehi, Surkhet and Rolpa- based on ecological belt and development region (Fig. 1).

**Fig. 1 Fig1:**
[figure not shown]
Location of study sites. Seven Ayurveda Health Centers are selected from Ramechhap, Dhading, Nuwakot, Kaski, Rupandehi, Surkhet and Rolpa Districts

### Study participants

Study participants will include hypertensive patients with or without anti-hypertensive medications attending DAHCs. Inclusion criteria include a SBP between 130 and 159 mmHg and/or DBP between 85 and 99 mmHg. Following are the sample selection criteria in detail.

#### Inclusion criteria

Age between18 years and 70 yearsBP criteria: SBP of 130 to 159 mmHg or DBP of 85 to 99 mmHg3 months or more of prescribed antihypertensive medication or without previously prescribed anti-hypertensive medicationsAttending to DAHCs

#### Exclusion criteria

Person having diabetes (self-reported) and mental diseasesPregnant womenKnown secondary cause of hypertension (self-reported)Hypertension (SBP ≥160 mmHg or DBP ≥100 mmHg)Practicing yoga more than one month in the previous 6 months

### Intervention

The intervention consists of three components: a) five days of yoga training (two hours per day); b) two hours health education session on healthy lifestyles; and c) home based self-practice of yoga daily for 90 days (with daily session lasting for 30 min). The treatment arm participants will receive all the intervention components whereas the control group will only be given the two-hour health education program and standard clinic care. Before the intervention, District Ayurveda Health Center staff (one from each center) will be orientated on yoga intervention packages and health education for high blood pressure prevention.

Structured yoga program contains yoga postures, breathing exercise and meditation (Table 1). Studies have used different regimens and elements of yoga intervention such as warm-up exercise [15, 16], postures [17–20], breathing [15, 18–20], Om recitation [16, 17, 20], relaxation [20, 21] and meditation [17, 18, 21] in single or combination generally for 30 min per day [15] for three months [9]. Hagins et al., in their systematic review suggested to integrate three elements of practice (posture, meditation, and breathing) as a single component. This combination of yoga practice was associated with significant reductions in blood pressure whereas yoga interventions using two or fewer elements of yoga practice or that combined yoga practice with additional interventions were not [14]. The intervention package in the current study has been developed based upon the recommendation from yoga therapists located in yoga centers in Nepal and aforementioned published studies [14]. Each yoga session takes 30 min to complete (Table 1). It starts with Om recitation (1 min), followed by warm up exercises (5 min), postures (4 min), relaxation (3 min), breathing (8 min) and meditation (9 min). One staff from each center will be trained in the yoga intervention package. The same person will deliver the yoga intervention to the high blood pressure participants. The study participants will receive a yoga training for two hours over five days at the allocated DAHCs. After the completion of training, participants in the treatment group will be requested to continue the practice at home once every morning for next 90 days. They will be invited for the regular follow-up to the centers once every 30 days. Participants will be asked to record the number of days they practice yoga using a calendar sheet to monitor progress and encourage accountability. During each follow-up day, outcome measurements (blood pressure and BMI) as well as qualitative assessment of home-based practice will be assessed.

**Table 1 Tab1:** Yoga module for the study participants

Sn	Practices	Rounds	Duration
1.	Starting with Omkar (Om recitation)	3	1 min
2.	Loosening exercise with synchronization of breathing in sitting position a) Toe bending b) Ankle bending c) Knee bending d) Half butterfly e) Finger bending f) Wrist bending g) Elbow bending h) Shoulder rotation i) Neck bending up and down	1 for each	5 min
3.	Ardhakatichakrasan (Lateral Arc Pose)		2 min
4.	Vakrasana (Twist Pose)		2 min
5.	Yogic abdominal awareness, breathing and feeling in Shavasana		3 min
6.	Chandravedi Pranayam (Left nostril breathing)	9 rounds	2 min
7.	Sheetali Pranayam (Cooling breathing)	9 rounds	2 min
8.	Nadi Suddhi Pranayama (Alternate Nostril breathing)	9 rounds	2 min
9.	Bhramari (Humming bee breathing**)**	9 rounds	2 min
10.	Yoga nidra (Yogic sleep)		9 min
	Total Time		30 min

Health education group counseling session (a single 2-h workshop) will be organized for both intervention and control groups. The course curriculum and contents have been adopted from the health education materials endorsed by National Health Education Information and Communication Center (NHEICC), Ministry of Health, Nepal. It contains behavioral and lifestyle modification education designed to reduce an exposure to the risk factors of hypertension like alcohol consumption, smoking, physical inactivity, and fat and salt reduction in diet (Table 2).

**Table 2 Tab2:** Health education module for the study participants

Sn	Chapter	Contents	Method	Media/tools	Time (Min)
1	Assessing level of understanding about hypertension among participants	Assessing paticipants’ knowledge on hypertension and its risk factors, complications and management	Brainstorming		15
2	A brief introduction on high blood pressure	Understanding the meaning of high blood pressure and its burden in Nepal	Interactive lecture	Drawing paper Marker	10
3	Risk factors of high blood pressure	Causes, non-modifiable risk factors, modifiable risk factors	Interactive lecture	Drawing paper Pictures, cartoon, Marker	10
4	Complication of high blood pressure	Complications of high blood pressure	Interactive lecture	Drawing paper Picture showing complication, Marker	10
	Break				15
5	Behavioral approaches for the management of high blood pressure	Healthy eating, nutritional recommendation based on Dietary approaches to stop hypertension (DASH), physical activity, maintaining healthy weight, limiting (or avoid) alcohol, quitting tobacco, reducing stress, tips for changing daily life	Interactive lecture, sharing of success case study	Drawing paper Pictures, Marker	60

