### Outcomes

The primary outcome of this trial will be the change in systolic blood pressure. It will be measured before, on each month interval and after completion of the intervention (at 90 days) at outpatient clinical settings with an aneroid sphygmomanometer (BP set). The secondary outcome will be the body mass index (BMI) and heart rate (HR). Both will be assessed at baseline and after the intervention.

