#### Clinical measurement

Blood pressure will be measured with an aneroid sphygmomanometer (BP set) in outpatient settings. Before taking the measurements, participants will be requested to rest for 15 min with legs uncrossed. Three readings of the systolic and diastolic blood pressure will be recorded in each five-minute interval. The average of second and third readings will be used for analysis.

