## Discussion

Hypertension is emerging as one of the major public health concerns in Nepal. Risk factors survey of the non-communicable disease (NCD) reported that 25.7% of all study population had hypertension [28]. Similarly, large proportions of hypertensive participants often have uncontrolled blood pressure [29].

Global action plan for the prevention and control of non-communicable diseases envisages for a 25% relative reduction in the prevalence of raised blood pressure in the next 10 years. Nepal has a well formed contextualized plan [30]. Interestingly, yoga as a health promotion measure has been recently established via the Urban Health Promotion Centers. Similarly, Department of Ayurveda introduced five days of yoga training to its sub-centers’ staffs for integrating yoga in prevention and control of NCDs. However, we still do not have sufficient evidence on the effect of yoga on hypertension prevention and control in Nepalese community. Therefore, this study expects to generate evidence that will be widely applicable for assisting blood pressure control and well-being in clinical and community settings in Nepal. It will be conducted in existing primary healthcare settings where the intervention package will be delivered by the government staffs at their respective OPDs. Such real-life routine practice settings for intervention would possibly increase the likelihood of generability and applicability of the study findings [31]. If proven effective, yoga can be integrated with medication as an adjunctive therapy for blood pressure control in similar low resource settings of Nepal and developing countries.

This study is not designed to determine which components of the yoga intervention will have an effect on blood pressure. To minimize errors in blood pressure measurement, data enumerators (medical persons) will be uniformly trained in blood pressure measurement including proper timing and positioning of the cuff and the patient.

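### The primary outcome is read by a person in a non-blinded trial, on the day home yoga practice is reviewed, and no stated safeguard addresses the reader's knowledge of the arm

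*Protocol article*

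**What the plan says.** The Trial design section states: "It will be a randomized, two-armed, non-blinded, pragmatic trial". It makes no exception for whoever measures the outcome. Under Outcomes, "The primary outcome of this trial will be the change in systolic blood pressure", measured at baseline, monthly and at 90 days.

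On the instrument, Clinical measurement says: "Blood pressure will be measured with an aneroid sphygmomanometer (BP set) in outpatient settings". The same section asks for 15 minutes of rest and three readings five minutes apart, and then: "The average of second and third readings will be used for analysis".

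On the visits, the Intervention section says of the yoga arm: "They will be invited for the regular follow-up to the centers once every 30 days". It continues: "During each follow-up day, outcome measurements (blood pressure and BMI) as well as qualitative assessment of home-based practice will be assessed".

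On staff, the Intervention section has one person per centre trained in the yoga package, and "The same person will deliver the yoga intervention to the high blood pressure participants". The Discussion assigns the measurement of blood pressure to a role with a different name: "data enumerators (medical persons) will be uniformly trained in blood pressure measurement including proper timing and positioning of the cuff and the patient". Data and safety monitoring adds a team that reviews the quality of data collection.

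**The concern.** An aneroid value is a human judgement from a moving dial. If the reader knows the arm and expects yoga to work, small choices in where to read or how to round can lean one way in one arm. Such a lean goes directly into the between-arm difference. Participants cannot be masked to yoga, but the person reading the dial can at least be kept from hearing about practice beforehand.

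The setting makes the concern plausible. Each centre has 20 participants, 10 per arm. Those in the yoga arm attend five training days at that centre, and the Study settings section describes a department that is training its own staff so that yoga can be built into its services. What is at stake is the credibility of a positive result. A modest true effect and a modest reading bias would look the same in the data.

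**Working it through.** **1. Which safeguards are stated, and what each one does.**

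| Safeguard | Section | Error it limits | Deals with knowledge of arm? |
|---|---|---|---|
| Uniform training of enumerators | Discussion | Technique | No |
| 15 minutes of rest, legs uncrossed | Clinical measurement | Technique, participant state | No |
| Three readings, mean of the last two | Clinical measurement | Random error | No |
| Quality-assurance team | Data and safety monitoring | Missing data, data errors, process | No |

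If one unmasked reader adds a shift b to both readings, their mean is also shifted by b. In the mixed model (Data management and analysis), a shift that follows the arm cannot be told apart from the arm effect. Monthly readings matter as well: last observation carried forward brings earlier follow-up values into the primary analysis for participants who drop out or change medication.

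**2. The plan's own sample size.** Inputs from Sample size: difference 7 mmHg, SD 13 mmHg, 80% power, 5% level, 20% dropout. The test is two-sided (Data management and analysis).

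- Normal approximation: n = 2 × (1.960 + 0.842)² × 13² / 7² = 54.1, so 55 per arm. Then 55 / 0.8 gives 69 per arm, 138 in total.
- t-test version: 55.1, so 56 per arm. Then 56 / 0.8 = 70 per arm, 140 in total.

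The stated 140 is reproduced. It implies 56 completers per arm.

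**3. Sensitivity to a reading shift.** The documents give no size for observer bias, so b is assumed. For a simple two-sample comparison with no true effect:

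- SE = 13 × √(2/56) = 2.46 mmHg. The smallest significant difference is 1.96 × 2.46 ≈ 4.8 mmHg.
- P(significant) = Φ(b/SE − 1.96) + Φ(−b/SE − 1.96).
- Example, b = 2: b/SE = 0.814, so Φ(−1.146) + Φ(−2.774) = 0.126 + 0.003 = 0.129.

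| Assumed shift b (mmHg) | Share of 7 mmHg | False-positive rate, 56 per arm | False-positive rate, 70 per arm (SE 2.20) |
|---|---|---|---|
| 0 | 0% | 5.0% | 5.0% |
| 1 | 14% | 6.9% | 7.4% |
| 2 | 29% | 12.9% | 14.9% |
| 3 | 43% | 23.1% | 27.7% |

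**The case against.** The trial openly calls itself non-blinded and pragmatic, and it claims no masking that it lacks. This is therefore a criticism of design and not a contradiction in the text. That stands. So does the point that a condensed article may leave the running order of a visit and the assignment of staff to the full protocol. The point does not rest on that silence alone: the article itself fixes a manually read outcome, no blinding, and practice review on the same day.

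Several stronger readings are tempting, and the documents do not support them:

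- **That the yoga instructor takes the blood pressure.** The article gives delivery to one trained person per centre and measurement to data enumerators. It does not say whether these overlap.
- **That practice is discussed before the reading, or by the same person.** Only the same day is stated.
- **That training is the only safeguard.** Rest, repeated readings, averaging and quality review are also stated.
- **That the reading is by auscultation.** The word does not appear. What is stated is an aneroid device, which a person must read in any case.
- **That a bias of 1 to 3 mmHg is likely.** Nothing in the documents supports any size or direction.

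It is also fair to say that the calculation is not the planned test. The plan is an intention-to-treat analysis with values carried forward, in a baseline-adjusted mixed model, so neither 56 per arm nor an SE of 2.46 is exactly that of the analysis. The column for 70 per arm shows that keeping everyone in the comparison makes it slightly more sensitive to a shift, not less.

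**Conclusion.** The concern holds as a gap in protection against observer bias, not as evidence that bias will occur. A primary outcome that depends on a person's reading is collected without blinding, on the day when the yoga arm's practice is reviewed, and every stated safeguard targets a different kind of error. If the reader's expectation moved the readings in one arm, no planned analysis would detect or remove it.

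The size is unknown. The rise from 5% to about 7%, 13% or 23% shows only how sensitive the comparison would be. It assumes a constant shift of 1, 2 or 3 mmHg between arms, SD 13 mmHg, 56 completers per arm and a simple two-sample test. The change is worth making because it costs little. The gap does not invalidate the design, and the sample size of 140 is unaffected.

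**What to change.** In the Intervention and Clinical measurement sections, state that:

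1. at every follow-up visit the blood pressure readings are taken and written down before the calendar or home practice is discussed;
2. the reader is one of the data enumerators already trained for the study, is not the yoga instructor and, as far as the centre allows, is not told the arm;
3. participants are asked not to mention their arm before the reading;
4. the same type of device is used at all centres and all visits;
5. where the reader cannot be masked, this is reported as a limitation.

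The cost is a fixed visit order and a division of roles among staff already in the plan, with some scheduling care at small centres. Masking will be incomplete: local staff enrol the participants, a participant list is shared with each centre, and the yoga arm trains on site. Full masking should therefore not be promised. Nor should a centre switch to an automated device only where it happens to own one. The documents do not say that any centre has one, and the instrument for the primary outcome would then differ between centres.
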